## Methods

### Objectives

The primary objective of this study is to evaluate diagnostic accuracy measures of tear biomarkers to discriminate participants with and without neurodegeneration as determined by hippocampal atrophy. The secondary objective is to determine the level of agreement between Aβ and tau protein levels in tear fluid, blood and CSF or PET. Thirdly, we aim to investigate whether the combination of retinal biomarker with tear biomarkers can aid in determining the presence of neurodegeneration as determined by hippocampal atrophy. The final objective is to analyze how biomarkers in tear fluid alter over the course of the follow-up period.

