### Outcome measures

Relation between tau protein levels in tear fluid and neurodegeneration determined by hippocampal atrophy.The level of agreement between Aβ biomarkers in tear fluid and Aβ positivity as determined by PET or CSF.The level of agreement between Aβ and tau protein levels in tear fluid, blood and CSF.The combination of retinal biomarkers and tear biomarkers as a predictor for neurodegeneration determined by hippocampal atrophy.Mean change in tear biomarkers between baseline, 12 months and 24 months.

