### Study assessments

Table 3 presents an overview and timing of the assessments. Follow-up visits are scheduled after 12 and 24 months.

**Table 3 Tab3:** Overview and timing of study assessments

Assessment	Baseline	12 months	24 months
In-/exclusion criteria	X		
Informed consent	X		
Medical history and medication	X	X	X
Routine neuropsychological tests^a^	X	X	X
CT or MRI scan^b^	X		
PET scan or CSF sampling^c^	X		
Blood sampling^d^	X		X
Routine ophthalmic examination^e^	X	X	X
Tear sampling^f^	X	X	X
Fundus imaging^g^	X	X	X
OCT imaging^h^	X	X	X

^a^ Neuropsychological assessment will be performed according to local routine protocol of memory clinic, as described elsewhere [19]. Covering the cognitive domains of global cognition, memory, attention, executive functioning and language

^b^ Images will be acquired with a 3 Tesla MRI-scan and 7 Tesla MRI for a small sub-cohort. The Scheltens MTA visual rating scale will be used to score each hemisphere (range 0–4) [22]. A summed score of both hemispheres will be defined abnormal with a cutoff of ≥ 2 [24]

^c^ CSF fluid will be available from a subset of participants and will be analyzed for Aβ 42, t-tau and p-tau-181 using an immunoassay, local cut-off values for each clinic will be used [20, 25]. A PET scan will also be available from a subset of participants, from which standard uptake value ratio (SUVr) images will be generated and visually read by an experienced nuclear physician. Images will be classified as positive or negative rating for Aβ according to criteria defined by the manufacturer (GE Healthcare) [26]

^d^ Participants will undergo venipuncture for blood sampling and subsequent analysis of Aβ42/40, t-tau and p-tau AD biomarker levels using immunoassays

^e^ The presence of potential ocular pathologies or unexpected findings will be assessed during the standard ophthalmic examination during which we will analyze visual acuity (using the Early Treatment Diabetic Retinopathy Study (ETDRS) chart (27)), (auto-) refraction, intraocular pressure (using non-contact tonometry), axial length (IOLMaster™, Carl Zeiss Meditec AG, Jena, Germany) and general eye health (using slit lamp biomicroscopy and funduscopy)

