### Statistical analysis

All data will be stored in the online database Castor EDC with restricted access [30]. The final data will be exported to IBM SPSS Statistics (IBM, Armonk, NY, USA) for statistical analysis. Data from participants with missing data or data from withdrawn participants will be included in the statistical analysis. Threshold of statistical significance will be assumed equal to p < 0.05.

Receiver operating characteristic (ROC) analyses will be performed to estimate the capability of tear biomarkers to differentiate between individuals with neurodegeneration and those without neurodegeneration as determined by hippocampal atrophy. The area under the curve and diagnostic accuracy measures such as sensitivity, specificity, predictive values and likelihood rations (with the corresponding 95% confidence intervals) will be calculated to assess the discriminative capability of a biomarker. To study the correlation of biomarker levels in tears, blood, CSF and PET will be performed using Pearson or Spearman correlation. Each biomarker will be separately compared across three body fluids, and the Aβ region of interest SUVr from PET. Based on our pilot results, we expect negative correlations between tears and CSF (similar to blood and CSF) [17]. Diagnostic accuracy will also be determined for the combination of tear and retinal biomarkers. Linear scores will be derived from the total area or partial area under the ROC curve. Lastly, we will study the mean change of tear biomarkers over time and how this correlates with disease progression (based on neuropsychological evaluation, imaging and fluid biomarkers) with the use of (generalized) linear mixed models or repeated measures ANOVA. Post hoc analysis will reveal which groups and time points differ significantly from each other.

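### The secondary objective is agreement, partly with a yes/no Aβ status, but the only analysis named for it is correlation of levels, so no stated analysis gives agreement with Aβ positivity

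*Protocol article*

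**What the plan says.** **Target.** Under Objectives, the secondary aim is to "determine the level of agreement between Aβ and tau protein levels in tear fluid, blood and CSF or PET". Outcome measures splits this into two: "The level of agreement between Aβ biomarkers in tear fluid and Aβ positivity as determined by PET or CSF", and "The level of agreement between Aβ and tau protein levels in tear fluid, blood and CSF".

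**Reference for Aβ positivity.** Table 3, footnote c, has PET images rated positive or negative by visual read and applies each clinic's own CSF cut-offs. CSF and PET each exist for a subset only. Study design and setting adds that amyloid PET is available in Amsterdam but not in Maastricht.

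**Method.** Statistical analysis says: "To study the correlation of biomarker levels in tears, blood, CSF and PET will be performed using Pearson or Spearman correlation". It continues: "Each biomarker will be separately compared across three body fluids", with the regional SUVr as the PET variable. On direction it states that "we expect negative correlations between tears and CSF", and likens this to blood and CSF.

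**ROC analysis.** The same section describes ROC curves, sensitivity, specificity, predictive values and likelihood ratios for separating participants with and without neurodegeneration, as determined by hippocampal atrophy.

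**Panels.** For CSF, footnote c lists Aβ42, "t-tau and p-tau-181 using an immunoassay". Footnotes d and f list Aβ42/40, t-tau and p-tau for blood and for tears. The abstract lists Aβ38, Aβ40, Aβ42, t-tau and p-tau for tears.

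**The concern.** Agreement and association are different quantities. Two measurements can correlate perfectly and still disagree in level, and a correlation between two continuous variables says nothing direct about how often one of them classifies a yes/no status correctly. The plan asks for agreement, once between levels and once with a binary status, and answers both with a correlation coefficient.

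The gap matters most for Aβ positivity. The article's case is about screening and diagnosis of AD, its Background treats Aβ deposition and neurodegeneration as separate biomarker categories, and Aβ positivity is the only AD-pathology status that it sets as a reference for an outcome. If the plan is run as written, the report would contain a correlation where readers expect sensitivity and specificity, and a small p-value could be presented as agreement.

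Two lesser problems sit beside this. The expected sign of the tear–CSF correlation is the opposite of agreement between levels. And the promise to compare each biomarker across three fluids does not fit the listed panels.

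**Working it through.** **1. The plan's own figure.** The only sample-size figure is for the primary outcome: n = 1.96² × 0.5 × 0.5 / 0.10² = 96.04, rounded up to 97 per group. It reproduces, but it concerns groups defined by atrophy. No figure is given for agreement or for the size of the CSF or PET subsets.

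**2. Outcome against analysis.**

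| Stated target | Type of reference | Analysis named | Does it give the target? |
|---|---|---|---|
| Neurodegeneration | Binary (MTA rating) | ROC, sensitivity, specificity | Yes |
| Tear + retinal markers for neurodegeneration | Binary (MTA rating) | Diagnostic accuracy of the combination | Yes |
| Tear Aβ with Aβ positivity | Binary (PET read or CSF cut-off) | Correlation with levels and SUVr | No |
| Levels in tears, blood, CSF | Continuous | Correlation | Association only |

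The sentence on the tear–retina combination does not repeat its reference, but Objectives and Outcome measures both tie it to hippocampal atrophy. It cannot be read as covering Aβ status.

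**3. Negative correlation and agreement of levels.** Lin's concordance coefficient is CCC = r × C_b, with 0 < C_b ≤ 1, so it takes the sign of r. The documents give no r; the values here are assumed.

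- r = −0.3: CCC lies between −0.30 and 0.
- r = −0.5: CCC lies between −0.50 and 0.

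If both markers are split at their medians (bivariate normality assumed), the proportion classified the same way is 0.5 + arcsin(r)/π, and kappa = (proportion − 0.5)/0.5.

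- r = −0.3: 40.3% the same way, kappa −0.19.
- r = −0.5: 33.3% the same way, kappa −0.33.

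Conversely, r = 1 with one fluid's values k times the other's, and mean/SD = 2 (assumed), gives CCC = 2k / [1 + k² + (2(k − 1))²]:

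- k = 2: 4 / (1 + 4 + 4) = 0.44.
- k = 10: 20 / (1 + 100 + 324) = 0.05.

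So a negative r excludes agreement of levels, and even a perfect positive r does not establish it.

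**4. Association and classification (illustration only).** Assume a binormal marker with equal variances and equal groups. Then d = √2 × Φ⁻¹(AUC), the point-biserial correlation with status is r = d/√(d² + 4), and sensitivity = specificity = Φ(d/2) at the midpoint cut-off.

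| Assumed AUC | d | r | Sensitivity = specificity |
|---|---|---|---|
| 0.65 | 0.545 | 0.26 | 61% |
| 0.75 | 0.954 | 0.43 | 68% |
| 0.85 | 1.466 | 0.59 | 77% |

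At AUC 0.75, 32% are misclassified although r is 0.43. This r is with binary status, whereas the plan correlates with levels and SUVr. The table therefore shows only that a correlation is not an error rate; it does not predict the study's result.

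**5. Precision of a correlation (r = 0.3 and the subset sizes are assumed).** By Fisher's z, tanh(arctanh 0.3 ± 1.96/√(n − 3)) gives −0.11 to 0.62 at n = 25, 0.02 to 0.53 at n = 50, and 0.11 to 0.47 at n = 100. A p-value alone would hide this spread.

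**6. Panels.**

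| Marker | Tears | Blood | CSF |
|---|---|---|---|
| t-tau | listed | listed | listed |
| p-tau | listed | listed | listed (181) |
| Aβ42 | abstract: separate; footnote f: within 42/40 | within 42/40 | listed |
| Aβ42/40 | listed | listed | cannot be formed |
| Aβ40 | abstract: separate | within 42/40 | not listed |
| Aβ38 | abstract only | not listed | not listed |

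The tau markers can be compared across three fluids, and Aβ42 can be if it is reported on its own in tears and blood. Aβ42/40, Aβ40 and Aβ38 cannot.

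**The case against.** The strongest reply is that this is a condensed article. A full protocol (version 2.0) is mentioned but not shown, and one missing ROC line for a secondary outcome could sit there. On levels, Statistical analysis says openly that correlation is meant, so agreement is perhaps just a loose word elsewhere. The status data are collected in any case, so nothing is lost for good.

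Part of this stands. No information is destroyed, the primary outcome and sample size are untouched, and for levels the repair is mainly one of wording. But the article is not silent here: it names a method for this objective, and that method does not answer the question set in Objectives and Outcome measures. That is a mismatch within the document and not an omitted detail.

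A reader might infer more than the documents support:

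- *That a negative correlation makes tear markers useless for Aβ status.* It excludes same-direction agreement of levels only. A marker with reversed direction can classify well. The negative expectation is also stated only for tears–CSF and, by analogy, blood–CSF, and not for PET or tears–blood.
- *That Aβ status is the only AD-specific measure.* Background names tau tangles as AD pathology, and tau is measured in all three fluids.
- *That the three-fluid comparison fails altogether.* It fails for Aβ42/40, Aβ40 and Aβ38 only.
- *That local CSF cut-offs distort the correlations.* Cut-offs define status and do not enter a correlation of levels. They matter for an analysis against Aβ status.

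**Conclusion.** The point holds, at moderate severity. A listed secondary outcome, agreement of tear Aβ with Aβ positivity, has no stated analysis that can produce it: the named correlations use levels and SUVr, and the accuracy analyses have hippocampal atrophy as their only reference. For levels, the stated target is agreement, the method measures association, and the expected tear–CSF result would contradict the target. The panel mismatch is real but minor.

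The main conclusion rests on the text alone. The numerical illustrations rest on assumed correlations, AUCs, subset sizes and normality, none of which the article gives, and they show direction and scale only. It is not a critical fault, because the objective is secondary and the repair uses planned data.

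**What to change.** 1. **Aβ positivity.** Add the ROC analysis already described (AUC, sensitivity, specificity, 95% confidence intervals) with PET or CSF Aβ status as reference, in the subset that has it. Report it by reference type and by site, because CSF cut-offs are local and PET is available at one site only. State the subset sizes.
2. **Levels.** Replace agreement with association in Objectives and Outcome measures, and report the correlations with 95% confidence intervals. State the expected direction for each biomarker and pair of sources.
3. **Three-fluid comparison.** Limit it to t-tau, p-tau and, if reported separately in tears and blood, Aβ42. Compare Aβ42/40 between tears and blood only. Reconcile the tear panel in the abstract with footnote f of Table 3.

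The cost is one further analysis run on data already planned, some rewording, and a less ambitious claim for levels. No new samples, visits or participants are needed.

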### Sample size

Sample size is based on our main outcome measure, which is estimating the diagnostic accuracy of biomarkers in tear fluid to discriminate between participants with and without neurodegeneration as determined by hippocampal atrophy. The calculation of sample size is based on the width of the 95% confidence intervals of sensitivity and specificity, as well as recent pilot data from our group [16]. To obtain a margin of error of maximally 10% for sensitivity as well as specificity, 97 individuals with neurodegeneration and 97 without neurodegeneration will be required. This calculation is performed using an online calculator (http://statulator.com/SampleSize/ss1P.html), where an expected proportion (sensitivity and specificity) of 50% was used as this yields the largest sample size. The diagnostic accuracy will be based on baseline parameters. To correct for potential dropout during follow-up, we increased the total number of participants to 200. Within these groups, participants will be divided into subgroups based on the clinical diagnosis. We aim to include a 50 participants per clinical diagnosis in order to obtain sufficient data to study secondary outcomes.

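### The tear-plus-retina score is derived from ROC area in the only cohort described and is not compared with tears alone, so its AUC will be biased upward unless corrected

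*Protocol article*

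**What the plan says.** All references are to the protocol article.

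- **Combined score.** The third aim under Objectives is to learn "whether the combination of retinal biomarker with tear biomarkers can aid" in detecting neurodegeneration. Statistical analysis answers this by determining the accuracy of the combination, and adds: "Linear scores will be derived from the total area or partial area under the ROC curve". Two criteria, total and partial area, are left open. The number of retinal inputs is not given. Background speaks of an array of retinal variables, and the footnotes to the assessment table list several imaging methods.
- **Single markers.** Statistical analysis plans ROC curves, AUC, sensitivity, specificity, predictive values and likelihood ratios with 95% intervals. It gives no tear cutoff and no rule for choosing one.
- **Sample size.** "The calculation of sample size is based on the width of the 95% confidence intervals of sensitivity and specificity", with an assumed value of 50% and a 10-point margin.
- **Primary marker.** The primary objective is to "evaluate diagnostic accuracy measures of tear biomarkers to discriminate participants", in the plural. The first outcome measure is "Relation between tau protein levels in tear fluid and neurodegeneration determined by hippocampal atrophy", which is tau only.
- **Cohort.** Study population describes one cohort of 200, expected to split 100 and 100. No derivation or validation subset is mentioned.

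**The concern.** A linear score whose weights are tuned to ROC area in a set of participants will separate those same participants better than it separates new ones. The gap grows with the number of inputs. If the score's accuracy is read from the cohort that produced the weights, adding retinal variables raises the apparent AUC whether or not they carry information. The third objective could then be answered yes by construction, because no contrast with a tear-only score is laid down to expose this.

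The same mechanism acts more weakly on sensitivity and specificity. The sample size uses a binomial interval, which presumes a cutoff fixed before the data are seen. A cutoff read from the study's own ROC curve moves both estimates upward and costs coverage.

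The article also presents the study as validating earlier results and informing whether tear markers have added value. Re-optimised accuracy does not serve either purpose.

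**Working it through.** **1. The plan's own figure.** Inputs from Sample size: 95% confidence (z = 1.96), "To obtain a margin of error of maximally 10% for sensitivity as well as specificity", and "an expected proportion (sensitivity and specificity) of 50% was used as this yields the largest sample size".

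n = z² p(1−p) / d² = 1.96² × 0.5 × 0.5 / 0.10² = 96.04, rounded up to 97 per group.

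This matches the stated 97 and 97. With 100 per group the half-width is 1.96 × √(0.25/100) = 0.098, or 9.8 points. The formula holds for one test at a cutoff fixed in advance.

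**2. Combined score.** The article gives no number of inputs and no true AUC, so these are assumptions:
- 100 versus 100 participants.
- Independent normal inputs, of which one is informative (AUC 0.70 alone) and the rest are noise.
- Linear discriminant weights as the linear score, fitted and evaluated in the same participants.
- A Hanley-McNeil 95% interval and 1,500 simulated studies per row.

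True AUC means the AUC of the fitted score in new participants. The last two comparisons are simple differences from 0.700, the AUC of the informative marker alone.

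| Inputs | Apparent AUC | True AUC | Apparent gain | True gain | Interval coverage |
|---|---|---|---|---|---|
| 5 | 0.714 | 0.686 | +0.014 | −0.014 | 86% |
| 10 | 0.734 | 0.671 | +0.034 | −0.029 | 57% |
| 15 | 0.750 | 0.659 | +0.050 | −0.041 | 26% |
| 20 | 0.764 | 0.648 | +0.064 | −0.052 | 8% |

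In every row the added noise looks like a gain and is in truth a loss.

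Varying the strength of the informative marker, with 10 inputs:
- alone 0.60: apparent 0.657, true 0.561
- alone 0.80: apparent 0.821, true 0.781
- no signal at all: apparent 0.625, true 0.500

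Weights that directly maximise the empirical ROC area cannot have a lower apparent AUC than the discriminant weights in the same data, so this stand-in does not exaggerate the apparent figure.

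**3. One marker, cutoff chosen on the data.** Assumptions: 100 versus 100, a normal marker, the cutoff that maximises the Youden index, an ordinary single-proportion 95% interval, and two independent sets of 4,000 simulated studies. Ranges show the two sets.

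| True AUC | Mean AUC | Sensitivity too high by | Specificity too high by | Coverage, sensitivity | Coverage, specificity |
|---|---|---|---|---|---|
| 0.60 | 0.600–0.601 | 4.0 points | 3.4 points | 88–89% | 91% |
| 0.70 | 0.700 | 3.4–3.5 points | 2.8 points | 90–91% | 92–93% |
| 0.80 | 0.799–0.801 | 2.9–3.0 points | 2.4 points | 92% | 93% |

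The AUC itself is unbiased here, and its interval covers 94 to 95%. Only the cutoff-dependent measures move.

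**4. Primary marker.** Side by side, Objectives and Statistical analysis cover tear biomarkers in general, while the first entry under Outcome measures covers tau alone. Tau is itself two markers, total and phosphorylated. The passages do not agree on what the primary analysis is.

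**The case against.** The strongest reply is that this is a condensed article. Cutoff rules, interval methods and internal validation usually sit in the full protocol or analysis plan, which are not shown. That stands in part. The article never says that the score will be evaluated in the participants it was derived from, and names no interval method. A reader might infer that ordinary same-sample intervals are planned, but the text supports only a conditional statement: the bias arises unless a correction is made. What does not depend on silence is that the article sets out how the score is derived, leaves two criteria open, describes one cohort, and answers a question about added value with the accuracy of the combination.

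A second reply is that tear-only accuracy will also be reported, so both figures will be available. True, but setting an uncorrected combined AUC beside a nearly unbiased single-marker AUC is the misleading comparison shown above.

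Three stronger readings are tempting and are not supported:
- *That all reported AUCs will be inflated.* The AUC of a single marker named in advance is not. Inflation would need selection of the best marker, which the article does not announce.
- *That five markers at 0.05 give a 23% chance of a false finding* (1 − 0.95⁵ = 0.226). The primary aim is estimation, sized on interval width. No success rule based on any one significant marker is stated, and the article lists the tear markers differently in the Abstract and the assessment table. The figure carries little weight, and so does a formal multiplicity adjustment.
- *That the primary marker ought to be total tau.* The outcome says tau, which covers both forms. The choice belongs to the sponsor.

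**Conclusion.** The point holds for the combined score and, to a lesser degree, for sensitivity and specificity. With an informative marker of AUC 0.70 and 100 per group, the uncorrected combined AUC is too high by about 0.03 with 5 inputs (0.714 − 0.686), 0.06 with 10 (0.734 − 0.671) and 0.12 with 20 (0.764 − 0.648). The size depends heavily on the number of inputs, which the article does not state. Not every participant will have every measurement (Discussion), and a smaller analysis set would make the optimism larger.

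For a data-chosen cutoff the effect is modest beside the planned 10-point margin. The interval fault there is mainly a shifted centre rather than too little width. The 97 per group is correct for a fixed cutoff and needs no change on this account. The mismatch between the primary objective and the first outcome is a contradiction in the text and does not depend on any simulation.

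**What to change.** - State one criterion for the score, either total or partial AUC, and list the candidate inputs.
- Report the score's AUC corrected for optimism by bootstrap or cross-validation, repeating the whole derivation in each resample.
- Answer the third objective with the corrected difference in AUC between the combined score and tears alone, in the same participants.
- Fix the tear cutoff or the rule that selects it. If it is chosen from the data, compute the sensitivity and specificity intervals by a bootstrap that repeats the selection.
- Reconcile Objectives with Outcome measures on whether the primary analysis concerns tau or all tear biomarkers, and report the remaining markers as secondary.

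The cost is a few sentences of analysis text and modest computing. Reported accuracy will be slightly lower, and the resampling may need software other than SPSS. No extra participants or measurements are required.

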## Discussion

As the number of people affected by Alzheimer’s disease will grow in the upcoming years due to increased life expectancy, there is a need for an accurate, low-invasive and low-cost diagnostic test that could enable early diagnosis. Future therapies combined with earlier diagnosis can increase the chance for preserving cognitive functioning. When people with cognitive complaints are referred to a memory clinic, a biomarker test (PET scan or CSF puncture) is not always chosen, often due to the fact that they are expensive, invasive, or not available. Diagnosis with tear fluid could lower the bar to apply biomarker tests, since it is low-cost and less invasive. Additionally, tear fluid can be collected at the general practitioner where the patient presents first, enabling timely detection. Tear fluid collection also has the potential to be used for screening purposes, due to its minimally invasive nature.

One of the main strengths of our study is the wide range of information that will be available from the participants, ranging from neuropsychological to ophthalmic tests, which will thereby generate a deeply phenotyped cohort. Furthermore, this study combines measurements of tear and retinal biomarkers, which are both low-invasive methods that potentially complement each other. Potential limitations of our study are that participants may be lost for follow-up visits, due to declining to participate, emigration or study drop-out. Particularly patients with fast cognitive decline may be lost somewhere along the two year follow-up. Another limitation is that not all measurements and data will be available for all participants due to different standard procedures and available equipment per study location.

The TearAD study will be the first longitudinal study analyzing tear AD biomarkers in a large cohort. The first results of the TearAD study, expected by early 2025, will inform whether tear AD biomarkers have added value in the screening and diagnosis of AD.

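### Repeated measures ANOVA is left open for the longitudinal objective, and choosing it would not honour the plan's own commitment to include participants with missing visits

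*Protocol article*

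**What the plan says.** The last outcome in the protocol article (Outcome measures) is "Mean change in tear biomarkers between baseline, 12 months and 24 months". Tear sampling is scheduled at all three visits (Table 3).

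Under Statistical analysis, this change, and "how this correlates with disease progression (based on neuropsychological evaluation, imaging and fluid biomarkers"), is to be studied "with the use of (generalized) linear mixed models or repeated measures ANOVA". The text gives no rule for choosing between the two methods. The same section makes a general commitment: "Data from participants with missing data or data from withdrawn participants will be included in the statistical analysis". It names the software ("The final data will be exported to IBM SPSS Statistics (IBM, Armonk, NY, USA) for statistical analysis") and mentions no imputation.

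The Discussion lists loss to follow-up as a limitation and says who is likely to be lost: "Particularly patients with fast cognitive decline may be lost somewhere along the two year follow-up".

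**The concern.** Repeated measures ANOVA, as SPSS runs it in the general linear model procedure, works on one row per participant and needs every visit. Someone who withdraws after 12 months contributes nothing, although the baseline and 12-month tear samples have been taken and assayed. One of the two permitted methods therefore does not do what the section promises about participants with missing data.

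Two things are at stake if that method is used. The first is precision: collected visits are thrown away, in diagnostic groups planned at 50 each. The second is selection. The document expects loss to be related to cognitive decline, and it wants tear-marker change related to disease progression. If the two are linked, completers are a selected group for this very question, and their mean change differs from that of everyone enrolled.

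**Working it through.** **1. The plan's own figure.** For a margin of error of 10% at a proportion of 50%: n = 1.96² × 0.5 × 0.5 / 0.10² = 96.04, rounded up to 97 per group. This reproduces the Sample size section ("97 individuals with neurodegeneration and 97 without neurodegeneration will be required"), a total of 194. Raising 194 to 200 allows for (200 − 194)/200 = 3% dropout. No dropout rate is stated. This calculation concerns the primary objective. It is shown only because it is the one place where the plan puts a number on loss.

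**2. What listwise deletion would discard.** Assume a loss fraction d in each of the two follow-up intervals, with no return after a missed visit.
- People with all three visits: 200(1 − d)².
- Collected visits discarded: 200d × 1 (baseline only) + 200(1 − d)d × 2 (baseline and 12 months).

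| Assumed d | Complete | People dropped | Visits discarded |
|---|---|---|---|
| 5% | 180.5 | 19.5 | 10 + 19 = 29 |
| 10% | 162 | 38 | 20 + 36 = 56 |
| 15% | 144.5 | 55.5 | 30 + 51 = 81 |
| 20% | 128 | 72 | 40 + 64 = 104 |

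A mixed model keeps all of these people and visits.

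**3. Bias when loss follows cognitive decline.** Assume a true 24-month change of 0.50 and a marker slope SD of 0.3 per year. Let ρ be the correlation between marker slope and cognitive decline, and let all loss come from the fastest-declining fraction d. The completers' mean change then shifts by −2 × 0.3 × ρ × φ(z)/(1 − d), where z is the upper-d normal quantile and φ is the normal density.

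| Dropout d | φ(z)/(1 − d) | Shift | Bias at ρ = 0.2 | Bias at ρ = 0 |
|---|---|---|---|---|
| 10% | 0.1755/0.9 = 0.195 | −0.117ρ | −0.023, or −5% | 0 |
| 20% | 0.2800/0.8 = 0.350 | −0.210ρ | −0.042, or −8% | 0 |
| 30% | 0.3477/0.7 = 0.497 | −0.298ρ | −0.060, or −12% | 0 |

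**4. Bias when loss depends directly on the marker.** This was simulated with 200 participants, three visits and 400 replicates. Assumptions: intercept SD 0.8, slope mean 0.25 and SD 0.3 per year, residual SD 0.5. The 24-month visit was missing with log-odds rising by 1 per SD of the driver. Complete cases stand for the ANOVA. The comparator is a maximum-likelihood repeated-measures model on all observed visits.

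| Driver of dropout | Dropout | Complete cases | Likelihood model |
|---|---|---|---|
| None (random) | 10 / 20 / 30% | 0.498 / 0.500 / 0.496 | 0.498 / 0.499 / 0.495 |
| Observed 12-month change | 10 / 20 / 30% | 0.456 / 0.404 / 0.363 (−9, −19, −27%) | 0.505 / 0.500 / 0.504 |
| Unobserved slope | 10 / 20 / 30% | 0.445 / 0.400 / 0.345 (−11, −20, −31%) | 0.463 / 0.435 / 0.395 (−7, −13, −21%) |

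The likelihood model is essentially unbiased in the first two rows. In the third it reduces the bias but does not remove it.

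**The case against.** The strongest reply is that there is no outright contradiction. The mixed model is named first, and ANOVA is only an alternative. The commitment to include people with missing data is general. For the baseline analyses it can be met through baseline data, and for the longitudinal objective it can be read as pointing to the mixed model. How missing values are handled may be settled in a full protocol or analysis plan that is not shown. This stands in part: the conflict arises only if ANOVA is chosen and nothing is imputed. The point is nevertheless not a complaint about missing detail. The text endorses a method that, used in the ordinary way, breaks a commitment in the same section, and it leaves the choice open.

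A second reply concerns bias. A reader might infer that the estimated change will be biased toward zero. The documents do not support that. They expect loss of fast cognitive decliners, not of people with large tear-marker change, and the link between the two is itself a study question. With no link, only precision is lost. The direction also depends on the sign of the link. The Discussion names other reasons for loss too, such as emigration and declining to participate.

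A third reply is that the mixed model is no full cure, and that the Discussion already discloses selective loss. Both are true. Disclosure, however, does not stop the ANOVA option from discarding collected data.

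**Conclusion.** The concern holds in conditional form. One of the two listed longitudinal methods would not honour the inclusion commitment, and nothing in the text rules it out. If it is used without imputation, the loss of data follows whatever the cause of dropout: about 38 people and 56 visits at an assumed 10% loss per interval.

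Bias is a further possibility, not a certainty. With a true change of 0.50 and 10–30% dropout, it is zero if marker change is unrelated to the cause of loss, about 5–12% at an assumed correlation of 0.2, and roughly 10–30% when loss depends directly on marker change. All of these rest on assumed dropout, slopes and selection strength. They describe the scenarios run and are not bounds on what the trial will see.

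Two other inferences should be resisted. No calculation here separates the diagnostic groups, so nothing shows that bias would be largest in MCI or AD dementia. Nor would completers consist only of slow decliners, because many fast decliners would also complete.

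This should be fixed but is not critical. It affects only the final objective. The Sample size section bases diagnostic accuracy on baseline data, so the primary analysis is untouched.

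**What to change.** In Statistical analysis, delete the repeated measures ANOVA alternative (four words). Name the likelihood-based (generalized) linear mixed model, fitted to all available visits, as the longitudinal analysis. Add one sentence saying that it is valid under missing at random and only reduces bias if dropout depends on unobserved decline. A sensitivity analysis for informative dropout would be a sensible companion. The choice of covariates and covariance structure is optional detail and is not needed to resolve this point.

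The cost is close to nothing. The plan already names the model and SPSS provides it. Sample size, visits and data collection do not change.
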